#### Statistical analyses

All statistical analyses will be performed by a statistician blinded to the group allocation. Percentages will be calculated for dichotomous data and analyzed by the *χ*^2^ test. Continuous variables will be expressed as mean ± standard deviation and median (ranging from 25th to 75th percentiles) and analyzed with the *T*-test and Mann-Whitney rank sum test. The paired sample *t*-test is used for comparison of the same index. Spearman and Pearson correlation analyses are used for the correlation analysis of normal distribution variables and non-normal distribution variables, respectively. *P* < 0.05 is considered statistically significant. IBM SPSS Statistics 25 is used as our statistical software. Multiple imputation will be used for handling missing data.

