### Participants

Elderly patients are more vulnerable to PPCs, and the incidence of PPCs in patients over 60 years was 19.2% [26]. To facilitate TOF monitoring on the upper limb and enlist relatively older patients, we plan to enroll in total of 414 participants undergoing arthroplasty surgery under general anesthesia, according to the calculation of sample size.

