#### Lung ultrasound

It is reported that LUS may be used as the primary imaging technique to assess PPCs by distinguishing A lines, B lines, and other typical signs, to assess pulmonary conditions and enhance bedside decision making [31, 32]. In this trial, LUS will be performed on subjects also by Mindray ultrasound instrument (model No. Compass; Shenzhen Wisonic Medical Technology Co, Ltd., Shenzhen, China), before induction of anesthesia, 10 min after extubation, and 30 min after extubation, respectively, by the same anesthesiologist specifically trained in carrying out diaphragm and lung ultrasonography for 3 months.

Each hemithorax can be divided into 3 regions with the anterior and posterior axillary lines—anterior, lateral, and posterior—each of which can be divided into upper and lower parts, that is, 6 examination areas of each hemithorax. The scoring system distinguishes four ventilation patterns as follows: normal aeration (score of 0, presence of lung sliding with A lines and up to two isolated B lines), moderate loss of pulmonary ventilation (score of 1, no fewer than 3 dispersive B lines originated from the pleural cavity), severe loss of pulmonary ventilation (score of 2, multiple coalescing B lines), and pulmonary consolidation (score of 3). As a result, the score of the total lung ranges from 0 to 36. The higher the score, the worse the pulmonary condition, and for each region, the worst visible pattern was recorded.

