### Outcomes

#### Primary endpoint

The primary outcome will be the incidence of PPCs 30 days after surgery in neostigmine and sugammadex groups. Using conventional broad criteria for diagnosis of PPCs, any postoperative pulmonary abnormality that adversely affects the clinical course of a patient could be defined as a PPC, including acute respiratory distress syndrome (ARDS), atelectasis, bronchospasm, pleural effusion, pneumothorax, respiratory failure, respiratory infection, and various other forms of upper airway obstruction [33–35] (see Table 1 for more details of its definition). The PI will make a phone call on postoperative day 30 (POD30) to retrospectively check whether there have been PPCs after the surgery till now and make a detailed record of the symptoms, severity, and kind of PPCs on the CRFs.

**Table 1 Tab1:** Definition of postoperative pulmonary complications (PPCs) [36]

PPCs	Definition
**Acute respiratory distress syndrome (ARDS)**	Acute onset of hypoxemia (partial pressure of oxygen, arterial (PaO_2_)/fraction of inspired oxygen (FiO_2_) ≤ 300 mmHg) with new bilateral infiltrates in the setting of either a normal pulmonary arterial wedge pressure (PAWP ≤ 18 mmHg) or the absence of suspected of left atrial hypertension when PAWP was not available
**Atelectasis**	Collapse of the alveoli; lung opacification with a shift of the mediastinum, hilum, or hemidiaphragm toward the affected area; and compensatory over inflation in the adjacent non-atelectatic lung
**Bronchospasm**	Newly detected expiratory wheeze treated with bronchodilators
**Pleural effusion**	Chest radiograph demonstrating blunting of the costophrenic angle, evidence of displacement of adjacent anatomical structures, or (in supine position) a hazy opacity in one hemithorax with preserved vascular shadows
**Pneumothorax**	A collection of air in the pleural space (the area with no vascular bed surrounding the visceral pleura)
**Respiratory failure**	Postoperative PaO_2_ 60 mmHg on room air, a PaO_2_/FiO_2_ < 300 mmHg, or arterial oxyhemoglobin saturation measured with pulse oximetry < 90% and requiring oxygen therapy
**Respiratory infection**	Treatment with antibiotics for a respiratory infection, plus at least one of the following criteria: new or changed sputum, new or changed lung opacities, fever, and leukocyte count > 12,000/mm^3^

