#### Other parameters

Sedation scoring of patients (see Table 2 for the Observer’s Assessment of Alertness/Sedation Scale (OAA/S)), duration of hospitalization, year, gender, ASA physical status of patients, dosage of intravenous and inhaling sedative drug/analgesia drug/NMBAs, duration of surgery, and anesthesia.

**Table 2 Tab2:** The Observer’s Assessment of Alertness/Sedation Scale (OAA/S) [40]

Score	Responsiveness
**5**	Awake and responds to name, spoken in a normal tone
**4**	Lethargic response to name, spoken in a normal tone
**3**	Responds only after the name is called loudly and/or repeatedly
**2**	Responds only after the name is called loudly and after mild shaking of the body
**1**	No response after the name is called loudly with mild shaking

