#### Sample size calculation

There have been no large-scale studies to confirm the actual incidence of PPCs in patients over 60 years undertaking arthroplasty. Referring to previous literature, the incidence of PPCs is15.4%, 19.2%, and 48.3% in the elderly [18, 26, 41]. To make the results of our study more reliable, we use 15.4% for sample size calculation. The overall incidence is around 5% in all patients undertaking non-cardiac surgery with general anesthesia and endotracheal intubation [15]. The necessary sample size has been calculated using the statistical software PASS 15. The analysis shows that at least 207 patients per group will be necessary (with a 95% confidence interval (CI), a power of 90%, 20% loss of follow-up), that is, 414 patients in total.

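### The primary PPC comparison is a valid chi-square test, but it leaves baseline variables already collected before reversal unused and may give up a little precision

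*Protocol article*

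**What the plan says.** All references are to the protocol article.

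- **Primary endpoint:** "The primary outcome will be the incidence of PPCs 30 days after surgery in neostigmine and sugammadex groups". This is a yes/no outcome per patient.
- **Statistical analyses:** "Percentages will be calculated for dichotomous data and analyzed by the" chi-square test. P < 0.05 "is considered statistically significant". The article names no regression, stratified or covariate-adjusted analysis.
- **Other parameters:** the recorded items include "duration of hospitalization, year, gender, ASA physical status of patients". I read the entry for year as age.
- **Lung ultrasound:** a total score from 0 to 36 is taken before induction and twice after extubation. The section opens: "It is reported that LUS may be used as the primary imaging technique to assess PPCs".
- **Participants:** "Elderly patients are more vulnerable to PPCs".
- **Randomization, allocation, and concealment:** the only stratification factor named is the reversal drug, which is the treatment itself. No baseline risk factor is balanced by design.

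**The concern.** Age, ASA status and the pre-induction lung ultrasound score are all fixed before reversal, so the assigned drug cannot affect them. The article itself links older age to PPCs and presents lung ultrasound as a way to assess them. An unadjusted test leaves in the estimate whatever part of the outcome variation these variables could explain.

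Few events are expected, about 34 under the planning assumptions, so a modest gain in precision would be welcome. Standardised adjustment targets the same marginal risk difference as the unadjusted comparison, usually with equal or smaller variance. What is at stake is efficiency. The validity of the primary test is not in question.

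**Working it through.** **Inputs.** The control PPC rate comes from the Sample size calculation section: "we use 15.4% for sample size calculation". The other settings are "with a 95% confidence interval (CI), a power of 90%, 20% loss of follow-up", 1:1 allocation and 207 per group. The sugammadex rate is not labelled. I take the roughly 5% quoted in the same section, which is an assumption. As a second case I use 7.7%, half of 15.4%, from the upper end of the 30–50% relative reduction quoted in the Discussion. Two-sided 5% is assumed from the 95% CI.

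**1. Reproduce the plan's figure.** With unpooled variance:

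n = (1.960 + 1.282)² × (0.154 × 0.846 + 0.05 × 0.95) / 0.104² = 172.7 per arm.

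172.7 × 1.2 = 207.3, which matches 207. The sample size is therefore consistent with an unadjusted comparison, as the analysis section plans.

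**2. Power of the planned test.** After 20% loss, 207 × 0.8 gives about 165 per arm. Expected events are 165 × 0.154 = 25.4 and 165 × 0.05 = 8.3, about 34 in total.

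Power = Φ[(δ − 1.96 × √(2p̄(1 − p̄)/n)) / √((p₁(1 − p₁) + p₂(1 − p₂))/n)].

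- 15.4% vs 5%, n = 165: (0.104 − 1.96 × 0.0333) / 0.0328 = 1.18, power 88.1%.
- 15.4% vs 7.7%, n = 165: (0.077 − 1.96 × 0.0352) / 0.0349 = 0.23, power 59.1%.
- At 207 per arm the same formula gives 94.1% and 69.0%.

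**3. Gain by formula.** If the covariates correlate ρ with the outcome, both variances are multiplied by 1 − ρ². At n = 165:

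| ρ | 15.4% vs 5% | 15.4% vs 7.7% |
|---|---|---|
| 0 | 88.1% | 59.1% |
| 0.2 | 89.3% | 60.8% |
| 0.3 | 90.9% | 63.2% |
| 0.4 | 92.9% | 66.7% |
| 0.5 | 95.2% | 71.6% |

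At about 10% incidence, ρ = 0.3 needs a baseline-risk AUC of about 0.75, and ρ = 0.5 needs about 0.86.

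**4. Gain by simulation.** The chi-square test was compared with a logistic model standardised to a risk difference, using one composite baseline score, at 165 and 207 per arm and for both effect sizes (3,000 trials per setting). The prognostic strength is assumed.

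| Assumed AUC | Change in variance | Change in power (points) |
|---|---|---|
| 0.50 | about 0 | about 0 |
| about 0.64 | 1–3% lower | +0.5 to +1.5 |
| about 0.71 | about 5% lower | +1.6 to +3.2 |
| about 0.78 | 11–14% lower | +2.4 to +7 |

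The +7 is 58.9% to 65.9% (15.4% vs 7.7%, n = 165). Simulated chi-square power for 15.4% vs 5% is about 90% rather than 88.1%, because the normal approximation is slightly low here. With no treatment effect, type I error was 4.9–5.7% adjusted and 4.8–5.4% for chi-square.

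**5. The three-covariate model itself.** At 165 per arm with ASA as one numeric term, variance was about 1% higher when nothing was prognostic and 5–12% lower at moderate to strong prognostic value. Power changed by about 0 to +4.5 points, type I error was 4.5–5.5%, and at most 1 fit in 3,000 failed. With ASA as three categories (15/60/25% mix assumed), fitting failed in about 5%, 9% and 16% of trials at AUC 0.64, 0.71 and 0.77.

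**6. Scale.** A 5% variance reduction is worth 414 × 0.05 = about 21 patients.

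**The case against.** The strongest reply is that nothing here is wrong. The chi-square test is valid, the sample size was built for it, and chance imbalance under randomisation is already allowed for in the type I error and the confidence interval. That stands. A reader might infer that the unadjusted test is biased or invalid because no risk factor is stratified, but the documents do not support that.

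The second reply is that prognostic value is not shown, and this also stands. The article describes the elderly as a group and gives no age gradient within patients over 60, the only ones enrolled. It also excludes the extremely old and frail. It links no ASA class to PPCs. It treats lung ultrasound as an assessment tool, and its Discussion says there is not yet agreement on using it to diagnose PPCs. A reader might take the ρ = 0.5 row (+7.1 and +12.5 points) as the expected gain. It needs an AUC of about 0.86, and nothing in the article supports that.

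Third, adjustment is not entirely free: with about 34 events, separate ASA categories can leave empty event cells. This holds for three-category coding and is largely removed by a single ASA term.

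Last, the article condenses a fuller plan, which may contain an adjusted analysis. That is possible, but the article does state a method for binary outcomes, and this point concerns that stated choice.

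**Conclusion.** The point holds as a missed efficiency of minor weight. The planned test is sound but uses none of three pre-reversal variables that the trial already records.

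The likely size is about 0 to +3 power points at plausible prognostic strength (AUC up to about 0.71), and about +4 to +7 only if the covariates predict strongly (AUC about 0.78), mainly with the smaller treatment effect. If they do not predict at all, the cost is about 1% more variance.

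These figures rest on assumed prognostic strength, an assumed 5% or 7.7% sugammadex rate, two-sided 5% testing, and mainly 165 evaluable patients per arm. Leaving the plan as it stands would not invalidate the result. The assumed sugammadex rate matters far more for power (88.1% against 59.1%) and is a separate matter.

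**What to change.** Amend the Statistical analyses section before the first unblinding, which already reveals group membership as A or B:

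- **Primary analysis:** logistic regression of 30-day PPC on arm, age (continuous), ASA status and pre-induction total lung ultrasound score. Report the standardised (marginal) risk difference with a 95% CI and a robust standard error. A plain adjusted odds ratio would change the effect measure and should not replace it.
- **ASA coding:** one numeric term, or I-II versus III, fixed in advance.
- **Supporting analysis and fallback:** the unadjusted chi-square test, which becomes primary if the model does not converge.
- **Missing data:** the article plans multiple imputation, so state that the standardised estimate and its robust standard error are computed in each imputed data set and then combined.

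The cost is a short paragraph and a little more analysis work, with no new data, visits or patients.

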**Methods/design:**

In this prospective, double-blind, randomized controlled trial, patients of the American Society of Anesthesiologists Physical Status I–III, aged over 60, will be enrolled. They will be scheduled to undergo arthroplasty under general anesthesia. All patients will be allocated randomly into two groups, group NEO (neostigmine) and group SUG (sugammadex), using these two drugs for reversing rocuronium. The primary outcome of the study is the incidence of PPCs in the NEO and SUG groups. The secondary outcomes are the evaluation of diaphragm ultrasonography and lung ultrasound, performed by an independent sonographer before anesthesia, and at 10 min and 30 min after extubation in the post-anesthesia care unit, respectively.

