Evidence from many retrospective and observational cohort studies have suggested that PORC are associated with many adverse consequences which may contribute to postoperative pulmonary complications (PPCs) [14, 15]. Residual paralysis can cause weakness of the ventilatory muscles, inability to cough, dysfunction of upper airway patency, and impaired swallowing reflex, to increase the risk of hypoxemia, atelectasis, aspiration pneumonia, airway obstruction, and other postoperative pulmonary complications [16, 17]. Therefore, it has been suggested that reducing PORC may decrease the incidence of PPCs. PPCs are harmful and related to poor patient outcomes, especially in high-risk patients, such as elderly patients. The incidence of PPCs was reported to reach 48.3% in elderly patients after administrating neostigmine or without any antagonists [18]. Early and rapid diagnosis is crucial for subsequent treatment. Although thoracic computed tomography (CT) is considered the gold standard of diagnosing PPCs, limitations such as radiation exposure hazards and inconvenient transfer for critical illness patients make it difficult to be routinely performed. Multiple investigations have the evidence that lung ultrasound (LUS) can outperform CT in portability and convenience, and it has been validated as an alternative tool for assisting in detecting atelectasis, pulmonary effusion, and pneumonia, etc. [19, 20].

Sugammadex, the first γ-cyclodextrin drug, is a specific antagonist for neuromuscular block induced by rocuronium. It has been proved by many studies that sugammadex can give a rapid, complete, and long-lasting recovery of muscle strength [21–23]. Compared to neostigmine, sugammadex can minimize the occurrence of PORC and may have the potential to lower the incidence of PPCs [15, 24].

In this prospective double-blinded randomized study, we hypothesize that the incidence of PPCs is lower after reversal with sugammadex than with neostigmine. Considering the incidence of PORC, we postulate that it is lower after reversal with sugammadex than with neostigmine through diaphragm ultrasound. Although the lung ultrasound could not be a substitute for thoracic CT in discerning PPCs, we try to evaluate the difference of changes in lung ultrasound after reversal of neuromuscular block by sugammadex and neostigmine respectively.

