#### Diaphragm ultrasonography

Before induction of anesthesia, 10 min after extubation, and 30 min after extubation, the right hemidiaphragm of the patient will be evaluated by a specially trained and skilled sonographer (an independent anesthesiologist) using a wisonic ultrasound instrument (model No. Compass; Shenzhen Wisonic Medical Technology Co, Ltd., Shenzhen, China). The sonographer was specifically trained in carrying out diaphragm and lung ultrasonography for 3 months. We only observe and evaluate the right hemidiaphragm because the left one is less accessible and reproducible [27]. The enrolled patient will be placed on the bed in a semi-decubitus position, with the head of the bed raised 45°.

DE of the right hemidiaphragm can be explored by a low-frequency US transducer (convex or phased-array probe) placed along the midclavicular line or below the right costal margin, during respiratory maneuvers such as quiet breathing, voluntary sniffing maneuver, and deep inspiration [28]. DE (amplitude in cm, velocity in cm/s especially during sniffing) can be measured using M-mode ultrasonography. The velocity during the sniffing maneuver can be measured from the baseline to the point of maximum height of inspiration, partially reflecting the potential contractility of the diaphragm [29]. On the zone of apposition (ZOA) to the rib cage for the right hemidiaphragm, it is possible to measure the diaphragmatic thickness (DT) with a high-frequency linear array probe [27]. Diaphragmatic TF can thus be calculated as the ratio, thickness at end-inspiration (TFI) − thickness at end-expiration (TEE) divided by TEE [30]. The diaphragm can be distinguished on the graph by identifying the hyperechoic pleural and peritoneal layers, with these two layers enclosing the hypoechoic diaphragmatic muscle. Three uninterrupted and undisturbed respiratory cycles will be measured and averaged for DE or DT/TF.

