#### Secondary endpoints

The secondary outcome will be the incidence of PORC in the two groups 10 min and 30 min after extubation, using diaphragmatic ultrasound as the method of appraisal. TF during a deep breath of 0.36 was considered as the threshold to exclude diaphragm dysfunction [8, 37–39]. According to our unpublished data, DE during deep breathing of 4 cm or less could also indicate diaphragmatic dysfunction. In this trial, PORC will be defined as TF ≤ 0.36 or DE ≤ 4cm.

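### No stated method adjusts the drug comparison of the continuous ultrasound measures for the pre-induction scan, and the paired t-test cannot make that comparison

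*Protocol article*

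**What the plan says.** **Schedule.** The Diaphragm ultrasonography section states: "Before induction of anesthesia, 10 min after extubation, and 30 min after extubation, the right hemidiaphragm of the patient will be evaluated". The Lung ultrasound section sets the same three times, "before induction of anesthesia, 10 min after extubation, and 30 min after extubation, respectively", and defines a whole-lung score from 0 to 36, higher being worse.

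**Question.** The Background puts the lung ultrasound aim as a contrast between drugs in change: "we try to evaluate the difference of changes in lung ultrasound after reversal of neuromuscular block by sugammadex and neostigmine respectively".

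**Methods.** Under Statistical analyses, continuous variables are "analyzed with the *T*-test and Mann-Whitney rank sum test". The only other comparison named for continuous data is "The paired sample *t*-test is used for comparison of the same index". Neither sentence names an outcome, a time point or a covariate.

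**Endpoints.** The abstract says "The secondary outcomes are the evaluation of diaphragm ultrasonography and lung ultrasound". The Secondary endpoints section says "The secondary outcome will be the incidence of PORC in the two groups 10 min and 30 min after extubation", and fixes the definition: "In this trial, PORC will be defined as TF ≤ 0.36 or DE ≤ 4cm". It does not list the lung score, and neither does Other parameters.

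**The concern.** The question is how two randomised arms differ on measures that each have a baseline and two follow-up values. Of the two tools named, the paired t-test looks only at change within a set of patients and gives no estimate of SUG minus NEO. The two-sample tests do compare arms, but nothing says that the pre-induction value enters them as a covariate.

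Two things are at stake. The first is precision: every patient is scanned before induction, and adjusting for that scan would narrow the interval for the drug difference at no cost in data. The second is interpretation: if paired tests are run arm by arm, a significant change in one arm and a non-significant change in the other can be mistaken for a drug effect.

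In addition, the abstract and the Outcomes section disagree on whether lung ultrasound is a secondary outcome. As the endpoint list stands, the lung score has no between-arm endpoint to which an analysis could attach.

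**Working it through.** **1. The plan's own figure.** The article gives no precision or sample size figure for the ultrasound measures. Its one figure, 207 per group, is for the primary endpoint. It is reproduced by an unpooled two-proportion formula with 15.4% v 5% (the text does not say that 5% is the SUG rate), two-sided 5% and 90% power: (1.960 + 1.282)² × (0.154×0.846 + 0.05×0.95) / 0.104² = 172.7, and 172.7 × 1.2 = 207.3. It is used here only to set a number of patients: 207 less 20% is 165.6, taken as 165 per arm.

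**2. Precision of three between-arm analyses.** Inputs:
- n patients per arm;
- equal SD (σ) at baseline and follow-up (assumed);
- baseline-to-follow-up correlation r, which the article does not give, so 0.3, 0.5 and 0.7 are assumed.

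The variance of the estimated arm difference is (2σ²/n) × k, where k is:
- post values only: k = 1
- change from baseline: k = 2(1 − r)
- ANCOVA on baseline: k = 1 − r²

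So ANCOVA relative to post values is 1 − r², and relative to change scores it is (1 − r²) / [2(1 − r)] = (1 + r)/2.

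| r (assumed) | k, post | k, change | k, ANCOVA | ANCOVA ÷ post | ANCOVA ÷ change |
|---|---|---|---|---|---|
| 0.3 | 1 | 1.40 | 0.91 | 0.91 | 0.65 |
| 0.5 | 1 | 1.00 | 0.75 | 0.75 | 0.75 |
| 0.7 | 1 | 0.60 | 0.51 | 0.51 | 0.85 |

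Both comparators are shown because the article does not say whether the two-sample tests are applied to follow-up values or to changes. The ratios do not depend on n.

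**3. The same in detectable differences.** At two-sided 5% and 90% power with 165 per arm, the post-value test detects (1.960 + 1.282) × √(2/165) = 0.357 SD. Multiplying by √k:

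| r (assumed) | post | change | ANCOVA |
|---|---|---|---|
| 0.3 | 0.357 | 0.422 | 0.340 |
| 0.5 | 0.357 | 0.357 | 0.309 |
| 0.7 | 0.357 | 0.276 | 0.255 |

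At r = 0.5, ANCOVA on 165 per arm is worth 165/0.75 = 220 per arm in either unadjusted analysis.

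**4. Why separate paired tests are no substitute.** Suppose the true change is identical in both arms and each arm's paired test has power p. Exactly one arm is then significant with probability 2p(1 − p): 0.42 at p = 0.3, 0.50 at 0.5, 0.32 at 0.8 and 0.18 at 0.9. The article gives no power for these tests, so this shows the hazard and does not forecast its size.

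**5. Endpoint lists.** The abstract's secondary outcomes cover diaphragm and lung ultrasound. The Secondary endpoints section covers PORC incidence only, from absolute TF and DE cut-offs after extubation. The pre-induction scan therefore enters no listed secondary endpoint, and the lung score is in none.

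**The case against.** The strongest reply is that the statistics paragraph is short and open.

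- The paired-test sentence does not mention ultrasound. TOFr before and after antagonism is also a repeated index. This stands, although the ultrasound measures are the ones taken at three times.
- The two-sample tests may be meant for changes. That would use the baseline scan and answer the Background's question. This also stands, and it is why both comparators are shown. It alters the gain from adjustment but does not remove it.
- Unadjusted two-sample tests are valid after 1:1 randomisation, and adjustment is often left to an analysis plan, which is not shown here. Validity is granted. But the article does state its methods, and none of them adjusts. The point concerns what those methods can deliver, not a missing detail.
- The lung score is bounded and has a floor at 0. If pre-induction scores sit near 0, r may be low and a linear model may fit poorly. This is fair, so the fix includes a rank-based check.
- The body's listed endpoints are binary and go to the χ² test. This is correct and limits the reach of the point. But the abstract names ultrasound evaluation as a secondary outcome, and the Discussion treats DE and DT/TF as endpoints.

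A reader might go further and infer that the trial plans to judge the drugs by setting one arm's paired p-value against the other's. The article does not say so. It names between-group tests, and a paired test may sit beside them as description.

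**Conclusion.** The point holds as a moderate recommendation. The paired t-test cannot estimate a drug difference, and none of the stated methods adjusts the between-arm comparison of DE, TF or lung score for the pre-induction scan. For r between 0.3 and 0.7, adjustment would reduce the variance by 9% to 49% against a post-value test, or by 35% to 15% against a change-score test. These figures rest on an assumed r, equal SDs and a roughly linear relation; the article supplies none of these.

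Three stronger conclusions are tempting but not supported. The text does not show that the baseline scan goes unused, because a test on changes is compatible with it. It does not show that the planned tests are invalid; they cost precision. Within-arm conclusions are a risk to be ruled out, not a stated plan.

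The mismatch over the lung score between the abstract and Secondary endpoints is plain from the text and needs no assumption. The primary endpoint, its sample size and the χ² comparison of PORC are untouched.

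**What to change.** 1. For DE, TF and lung score, state that the SUG minus NEO difference at 10 and at 30 min will be estimated by ANCOVA, or by one mixed model over both times, with the pre-induction value as covariate and a 95% CI.
2. For the lung score, add a rank-based sensitivity analysis because the scale is bounded.
3. Say which indices the paired t-test covers, and that it is descriptive and will not be used to compare the drugs.
4. List the lung score at 10 and 30 min under Secondary endpoints so that the section agrees with the abstract.

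The cost is a few lines of wording. No new data are needed, and the named SPSS package fits these models. The price is some reliance on a linear model for the lung score, which item 2 addresses. The wording should be settled before the first unblinding, so that results cannot steer the choice.

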Ultrasonography is a novel and useful technique for the evaluation both in diaphragm function and pulmonary complications. Works of literature have suggested that ultrasonography is of good interobserver reproducibility and repeatability if the operator is well trained [29, 42]. DE or DT/TF as endpoints will be measured referring to recent studies of diaphragm ultrasound. We simultaneously perform TOFr monitoring and diaphragm ultrasound in the study for the purpose of verifying that diaphragm recovery may be still insufficient despite adequate peripheral TOFr. Lung ultrasound will be facilitated to detect atelectasis, pneumonia, or pulmonary effusion, which are common pulmonary complications. Unfortunately, although some researches are indicating the high sensibility and specificity of LUS to diagnose atelectasis, pneumothorax, and pleural effusion [31, 32, 43], with a diagnostic accuracy of over 90% [43], there is no consensus on lung ultrasound to diagnose PPCs yet. We, therefore, aim to link the incidence of PPCs to lung ultrasound by analyzing the postoperative ultrasound imaging score and follow-up procedures straight into 30 days after their surgeries.

In summary, this randomized double-blind controlled trial may be the first study that provides important information on the comparison of incidence of PORC and PPCs between neostigmine and sugammadex through two novel and useful approaches, diaphragm ultrasonography, and lung ultrasound.

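### The correlation rule is inverted as written: Spearman is assigned to normal variables and Pearson to non-normal ones. This is probably a drafting slip, and it affects correlation analyses only

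*Protocol article*

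**What the plan says.** The protocol article gives one rule for correlations, in Statistical analyses: "Spearman and Pearson correlation analyses are used for the correlation analysis of normal distribution variables and non-normal distribution variables, respectively". The methods come in the order Spearman, Pearson and the variable types in the order normal, non-normal, and the last word pairs them in that order.

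The same section treats group comparisons of continuous variables in the conventional order, with the parametric summary and test first and the rank-based ones second: "Continuous variables will be expressed as mean ± standard deviation and median (ranging from 25th to 75th percentiles) and analyzed with the *T*-test and Mann-Whitney rank" (cut off here within the name of the second method). Dichotomous data go to the chi-squared test.

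No endpoint section names a correlation or a pair of variables to be correlated. The Discussion says that the authors "aim to link the incidence of PPCs to lung ultrasound by analyzing the postoperative ultrasound imaging score", without naming a method.

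**The concern.** Pearson's coefficient measures linear association, and its usual test is best suited to data that are roughly bivariate normal. Spearman's works on ranks and is the usual choice for skewed, bounded or ordinal data. The written rule assigns them the other way round.

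Some variables in this trial are non-normal by construction. The lung ultrasound total is a sum of twelve regional ratings of 0 to 3: "As a result, the score of the total lung ranges from 0 to 36". The OAA/S has five ordered levels. TOFr immediately before extubation is cut off from below, because extubation requires a value above 0.9. If any of these enters a correlation, the rule as written sends it to Pearson.

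At stake is the power and size of any reported correlation. There is also a reporting problem. An analyst who follows the rule uses the less suitable coefficient, and one who silently corrects it departs from the published plan on a choice that can move a result across the 0.05 line.

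**Working it through.** **Step 1: the wording.** The rule carries no figure, so there is nothing numerical in the plan to reproduce.

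| Order in the sentence | Method | Variable type | Usual choice |
|---|---|---|---|
| First | Spearman | Normal | Pearson |
| Second | Pearson | Non-normal | Spearman |

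Both rows are the reverse of the usual choice. No other section restates or corrects the rule.

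**Step 2: what the rule governs.** PPC incidence (primary) and PORC incidence (secondary) are yes/no outcomes and go to the chi-squared test. Group comparisons of continuous variables have their own sentence. Only correlation analyses depend on the rule.

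**Step 3: how much the reversal could cost.** This was simulated with 2,000 replicates per setting and a two-sided 0.05 level. The document gives 0.05 but not the sidedness. The model is x ~ N(0,1) and y = ρx + √(1 − ρ²)·e with e ~ N(0,1). Variables are then transformed to the assumed shape, and both coefficients are tested on the same data. The document gives 414 in total. The figure of 166 does not appear in it, although it matches one group after the stated 20% loss: 207 × 0.8 = 165.6. The values of ρ and all the shapes are assumptions. The Monte Carlo standard error at 95% power is √(0.95 × 0.05 / 2000) = 0.005, so differences of about one point carry little meaning.

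*Normal data, where the written rule gives Spearman:*

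| n, ρ | Spearman (as written) | Pearson (swapped) |
|---|---|---|
| 166, 0.2 | 70% | 74% |
| 414, 0.15 | 83% | 87% |
| 100, 0.3 | 81% | 84% |

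*Bounded non-normal data, where the written rule gives Pearson (n = 166, ρ = 0.3).* The lung score is taken as a negative binomial capped at 36.

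| Pair | Pearson (as written) | Spearman (swapped) |
|---|---|---|
| Lung score (mean 4, dispersion 2) with a normal index | 96% | 96% |
| Lung score (mean 4, dispersion 1) with a normal index | 95% | 95% |
| Lung score (mean 2, dispersion 0.7, piled at 0) with a normal index | 92% | 95% |
| TOFr flat on 0.9–1.0 with a normal index | 98% | 97% |
| TOFr skewed on 0.9–1.05 with a normal index | 97% | 96% |
| Lung score with skewed TOFr | 93% | 97% |

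Mean coefficients were 0.26–0.29 for Pearson and 0.27–0.29 for Spearman. With weaker correlations the largest gap for these bounded shapes was 61% against 68% (ρ = 0.2), and 77% against 83% at n = 414 and ρ = 0.15.

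*Heavily skewed data, both variables log-normal:*

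| Setting | Pearson (as written) | Spearman (swapped) |
|---|---|---|
| n = 166, ρ = 0.3, log SD 1.0 | about 71% | 96% |
| n = 166, ρ = 0.3, log SD 1.5 | about 41% | 96% |
| n = 414, ρ = 0.15, log SD 1.5 | 24% | 84% |

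In the last row the mean coefficient was 0.07 for Pearson and 0.14 for Spearman.

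*No correlation (ρ = 0; n = 100 and 414; normal and log-normal with log SD 1.5):* rejection rates were 0.039 to 0.061 across both coefficients.

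**The case against.** The strongest reply is that this is a slip that any statistician would recognise. The neighbouring sentence uses the conventional order, and nobody plans to use Pearson for skewed data. That is very likely true, and it explains the error. It does not remove it: the sentence is the only correlation rule in the document and has one literal reading. Nor is this a detail that a condensed article leaves to a fuller plan, because the article states the rule and states it wrongly.

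The second reply is that the harm is small, and most of this stands. Spearman on normal data is a valid analysis. Pearson did about as well as Spearman for most of the bounded shapes, and a TOFr confined just above 0.9 leaves little room for outliers. The large losses come from choosing an unbounded log-normal shape, which neither the lung score nor TOFr is shown to have.

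A reader might infer that the trial's association claims would be unreliable, attenuated and driven by outliers, with the wrong coefficient doing harm in both cases. The document does not support that. Only the Pearson half can do material damage, and only under heavy skew. A reader might also infer that the Discussion's aim of relating lung ultrasound to PPCs is compromised. That passage names no correlation, and because PPC is yes/no, a rule that turns on normality does not clearly govern it.

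**Conclusion.** The point holds as a correction to an operative analysis rule that is wrong as written, with limited consequences. The wording error is certain; that it is a slip is probable.

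The size rests on assumption. It is about 3 to 4 points of power for Spearman on normal data. For Pearson on bounded variables it is 0 to 4 points at n = 166 and ρ = 0.3, and up to 7 points in the weaker-correlation settings tried. Under log-normal skew the loss is large: 96 − 71 = 25 and 96 − 41 = 55 points. The document does not say how skewed its variables will be, so it cannot be known which case applies. No inflation of type I error was shown. The PPC and PORC comparisons and the sample size are untouched.

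**What to change.** Swap the two names in the sentence: Pearson for approximately normal variables, Spearman for non-normal or ordinal ones, for example the 0–36 lung score and the OAA/S. If the full protocol or analysis plan carries the same sentence, make the same change there, preferably before the data are unblinded, so that the choice cannot appear to follow the results.

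The cost is one sentence. Sample size, data collection and trial conduct do not change.
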